### Participants

#### Phase I: development phase

All adults (≥18 years) receiving specialist palliative care newly admitted
in 10 participating sites during the study period (two sites providing hospital
advisory services, one providing community-based service only, six providing
hospice inpatient and community-based services, one providing hospital advisory
and community-based services) were included, regardless of primary diagnosis. We
selected these sites with the aim of ensuring a representative sample in terms of
population demographics (age distribution, ethnicity, socioeconomic status and
rural/urban composition). Written informed consent was taken by a qualified member
of the research or clinical team. This phase included individuals with limited,
fluctuating, diminishing or lack of capacity, vital to ensure that any casemix
classification is applicable to all palliative patients, not just those able to
consent. It is recognised that a high proportion of those have impaired capacity,
and these patients may need palliative care and resources most.^20–23^ Therefore, if the
clinician assessed that the patient did not currently have the capacity to give
consent, assent was sought from an accompanying family member, or failing that, a
staff member to whom the patient was known. Where a formally appointed power of
attorney existed, this took precedence.

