#### Phase II: validation phase

All adults (≥18 years) receiving specialist palliative care newly admitted
from 14 sites during the study period (participating sites in phase I, but
extending to four additional sites to increase recruitment) will be eligible,
regardless of primary diagnosis. Additional sites were accepted if they could
contribute to maintaining or extending representativeness in terms of population
demographics (age distribution, ethnicity, socioeconomic status and rural/urban
composition). Written informed consent will be sought from eligible patients (and
their family caregivers) at the outset, including advance consent for study
follow-up if capacity is lost. This study is of minimal risk with participants not
exposed to undue harm.^24^

For both phase I and II, a list of study sites can be obtained via https://www.kcl.ac.uk/nursing/departments/cicelysaunders/research/studies/c-change/c-change.aspx.

Since transition of care is important for casemix, patient participants who
transfer between settings (and caregiver participants) will be followed up. We
will verbally confirm continuing consent with each participant when making such
contact. If capacity of patient participants is lost, we will seek advice from a
personal consultee on whether the patient should remain in the study to verify no
change of decisions has been expressed by the patient prior to loss of capacity.
On recruitment, participants will be asked if they are willing to be interviewed
at a later stage. To capture variation in age, gender, diagnosis and geographical
location, we will purposively select 20–25 patients and family caregivers
with at least two transitions of care for face-to-face interviews. Each
semistructured interview will last 40 min, but will be guided by each
participant. In order to provide information on how care transitions might be
better negotiated to improve outcomes and experiences, the interviews will cover
communication, coordination of care, information/support needs, discharge planning
and experience of transitions.

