#### Model of care

Models of care may be a stronger cost driver than patient-level variables.^13 14 16^ Specialist palliative care
services have various configurations of staff, interventions and other
characteristics. Currently, there is no consistent way to define models of
palliative care. A separate, parallel study will be conducted in which
service-level data including the numbers, disciplines and grading of staff, the
nature/duration of their involvement and use of volunteers will be collected to
comprehensively characterise different models of palliative care provision in the
participating sites. With findings from this step, a new categorical variable will
be created representing ‘model of care’ to be included in our
analysis.

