### Statistical analysis methods

We will use descriptive statistics including frequencies, mean and SD, and median and
interquartile ranges as appropriate to describe the sample characteristics and number
and length of episodes of care. Trajectory of outcomes and costs will be described,
comparing patterns in patients with cancer and without cancer, and contrasting
those with no unmet needs and those with unmet needs. We will compare our data with
existing phase and episode data from the Australian Palliative Care Outcome
Collaboration.^48^ In the Australian
classification, five casemix criteria (phase of illness, problem severity, functional
status and dependency, age, model of care) were found to be most strongly predictive
of resource use. If our analyses demonstrate the same five criteria as most
predictive of resource use, the Australian classification or a refinement of it will
be adopted. If there is disparity, then the data on individual casemix criteria will
be used to develop a new casemix classification, using a recursive partitioning
approach—specifically classification and regression trees^49 50^compared with multivariable regression (figure 1).

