### Model development

The distribution of casemix criteria (cost predictors) in the participant population
will be described based on phase of illness, functional status and problem severity,
using parametric or non-parametric statistics, as appropriate. In order to reduce the
number of cost predictors, we will initially use univariate analysis to explore the
association and strength of association between casemix criteria and cost of the
episode of care (quantifying cost by per diem cost, per phase cost and total cost of
episode). We will use generalised linear model (multivariate regression model) to
select variables that will then be applied in a hierarchical manner to form a
branching classification in which each cost driver is incorporated only once.

We will select variables according to how much of the predictive error
(R^2^) each variable predicts and the related P value. After each
bootstrap iteration, we will rank the variables according to these two criteria and
remove the weakest (non-significant) predictor. Variables shown in tables 2 and 3 and the newly created
categorical variable representing ‘model of care’ will be initially
entered into the models and then non-significant predictors removed at each iteration
using a Bootstrap subsampling strategy. We will create dummy variables to enable each
level of phase of illness and model of care (categorical variables) to be assessed
individually. Internal validation will be conducted by using such methods as
bootstrapping or cross-validation to quantify any optimism in the predictive
performance (calibration and discrimination) of the developed classification.

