**Figure 2 F2:**
[figure not shown]
Casemix classification specification.

Multilevel modelling will be undertaken to ensure that both of these steps
will be delivered in this study by determining (1) which casemix criteria are most
strongly associated with clinical outcomes, allowing for clustering at the level of
‘participant’ (where episodes occur in the same individual), at the
level of ‘model of care’ (where care is received according to similar
models), and at the level of ‘site’ (where care is delivered in a
similar way within site), and (2) which casemix criteria are the strongest cost
predictor (including per diem cost, per phase cost and total episode cost).

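### Model of care, a service-level variable, is selected as a cost driver on episode-level P values with no site term, although phase I holds only 3, 6 and 8 site-by-setting units

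*Protocol article*

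**What the plan says.** The Model of care section of the protocol article derives one new categorical variable from a parallel study of services. The inputs are described as "service-level data including the numbers, disciplines and grading of staff, the" and so on. The number of categories is not given.

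Model development names a generalised linear model as the tool that chooses variables for the classification. Variables are ranked on R² and P value at each bootstrap iteration and non-significant ones are removed. Dummy coding is planned for this variable, the stated aim being for each "level of phase of illness and model of care (categorical variables) to be assessed" on its own. No site or service term appears, and no resampling unit is named for the bootstrap.

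In Model specification, the paragraph after Figure 2 says that multilevel modelling will serve two steps. Step (1), on clinical outcomes, names three clustering levels: participant, site, and one worded "level of ‘model of care’ (where care is received according to similar". Step (2), on cost predictors, lists no levels.

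The phase I Participants section describes recruitment "in 10 participating sites during the study period (two sites providing hospital". By type, two sites are hospital only, one is community only, six combine inpatient hospice with community care, and one combines hospital advice with community care. Phase II keeps these sites, "extending to four additional sites to increase recruitment) will be eligible", without giving the settings of the new sites.

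Statistical analysis methods recalls five criteria from the Australian work, its list closing with "status and dependency, age, model of care) were found to be most strongly predictive". Whether the UK data show the same five bears on adopting or refining that classification, or building a new one.

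**The concern.** Every episode in a given service carries the same value of model of care. Comparing its categories is therefore a comparison of services, and the relevant error is the variation between services with the same model. A regression on episodes without a site term compares them against variation between episodes, which is divided by a much larger number. Any ordinary cost difference between sites, from case flow to recording habits, then tends to appear as an effect of model of care.

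This affects one of the five criteria that the plan compares with the Australian result, and one that the plan expects may outweigh patient-level variables as a cost driver. The multilevel paragraph could have settled the matter, but it leaves two things open: which levels the cost model has, and whether that model or the generalised linear model decides the cost drivers.

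**Working it through.** **Inputs from the protocol article.** Phase I site types are 2 hospital only, 1 community only, 6 hospice inpatient plus community, and 1 hospital plus community. The plan has 450 episodes per setting, with 25% incomplete and up to 10% of complete episodes cost outliers, at alpha 5%.

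**The plan's own totals reproduce.** 2 + 1 + 6 + 1 = 10 sites, and 450 × 3 = 1350 episodes. The 450 itself cannot be rederived because the number of predictors is not stated.

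**Units per setting.** Hospital 2 + 1 = 3; hospice inpatient 6; community 1 + 6 + 1 = 8. That is 17 units in 10 sites, with 6 + 1 = 7 sites supplying two units each (7 × 2 + 3 = 17).

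**Usable episodes per setting.** 450 × 0.75 × 0.90 = 303.75, about 304.

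**Assumptions, not in the document.** Site ICC 0 to 0.10, two categories with no true difference, equal unit sizes, no covariates, and a separate analysis per setting.

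**Formulas.** With n episodes per unit, the design effect is DE = 1 + (n − 1) × ICC. The true error rate of the episode-level test is about 2 × [1 − Φ(1.96/√DE)].

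Hospital at ICC 0.05: n = 304/3 = 101.3; DE = 1 + 100.3 × 0.05 = 6.02; 1.96/√6.02 = 0.80; error rate 42.4%.

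| Units | n per unit | ICC 0.02: DE, error | ICC 0.05: DE, error | ICC 0.10: DE, error |
|---|---|---|---|---|
| 3 hospital | 101.3 | 3.01, 25.8% | 6.02, 42.4% | 11.03, 55.5% |
| 6 hospice inpatient | 50.7 | 1.99, 16.5% | 3.48, 29.4% | 5.97, 42.2% |
| 8 community | 38.0 | 1.74, 13.7% | 2.85, 24.6% | 4.70, 36.6% |

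At ICC 0, DE = 1 and the error rate is 5%.

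**Simulation check.** With 20,000 data sets per scenario, 303 episodes, ICC 0.05 and splits of 1 v 2, 3 v 3 and 4 v 4, the episode-level test gave 43.2%, 29.6% and 24.1%. A t test on unit means gave 5.1%, 5.3% and 4.9%. Splits of 2 v 4 and 2 v 6 gave 28.9% and 24.2% for the episode-level test, so the split matters little.

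**What a valid test can do.** With two categories the between-unit degrees of freedom are k − 2 = 1, 4 and 6, with critical t of 12.71, 2.78 and 2.45. With three categories in hospital there are none. For a true difference of 0.5 SD at ICC 0.05, the episode-level test is significant in about 82%, 90% and 92% of runs. The unit-level test is significant in about 11%, 43% and 58%.

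**The case against.** The strongest reply is that the plan gives model of care different roles for different outcomes. The dummies are for cost, while the clustering list is worded within the step on clinical outcomes. A factor may be a predictor in one model and a level in another, and that part of the reply stands. Multilevel modelling is also said to cover cost, so the authors may intend site and participant as levels with model of care as a fixed effect. That reading is open, but the text does not state it, and the section that governs selection names a generalised linear model without a site term. If the clustering list does extend to cost, model of care yields a variance component but no per-level coefficient or P value to rank.

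Ranking also uses R², which is true. But non-significance is the stated ground for removal, and R² also absorbs site differences. The bootstrap does not help as written, because it names no site-level resampling and cannot create more services.

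The size of the inflation depends on the assumptions listed, and a site might run several teams within one setting. This stands as a limit on the figures, not on their direction.

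Random-effect detail is often left to an analysis plan. Here, however, the article itself fixes the selection rule, and that rule gives the wrong P value for this variable.

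**Conclusion.** The point holds for the stated selection rule. Followed as written, it judges a service-level variable against episode-level error. With 3, 6 and 8 units, the nominal 5% becomes about 26%, 16.5% and 14% at ICC 0.02, and about 43%, 29% and 25% at ICC 0.05. These figures rest on assumed ICCs, two categories, equal unit sizes and per-setting analysis. The unit counts are for phase I only. The multilevel paragraph leaves open the levels for cost and which model decides.

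Two stronger readings are tempting and not supported. A reader might infer that the plan makes model of care both a fixed predictor and a clustering level in the same cost model. The wording is ambiguous on this, not contradictory. A reader might also infer that the two analyses would give opposite answers on adopting the Australian classification or building a new one. That is not shown: the rule allows a refinement of the Australian scheme, internal and external validation follow, and the documents do not let one trace how a single retained or dropped factor would change the final classes.

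**What to change.** - For cost, state that the multilevel model replaces the generalised linear model for variable selection, with random intercepts for site, service within site, and participant. The site intercept is needed in a pooled model because seven of the ten sites supply two units each. Within a single setting, site and service coincide on the counts given.
- Resample by site in the bootstrap.
- Enter model of care once for cost, as a fixed factor and not as a clustering level. Test it as a whole on between-site or between-service degrees of freedom with a small-sample correction such as Kenward-Roger, outside the episode-level P-value ranking.
- Report it descriptively where there are too few units, as in hospital with three. Take any test from a model pooled over settings with a setting term.
- Do not rely on permuting service labels within a setting. A 3 v 3 hospice split has 20 arrangements, so the smallest two-sided P is 2/20 = 0.10.

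The change needs no new data, only analysis wording. It has a price: a pooled model departs from the per-setting sizing, resampling ten sites is coarse, and the model-of-care effect will have a wide interval and may not be declared a predictor.

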### Model specification

The casemix classification for each outcome across three settings will be presented
including all regression coefficients and model intercept (figure 2). How to use the classification will be explained.
Understanding how casemix variables predict cost of the episode of care enables a
robust casemix classification to be developed. But in order for casemix adjustment to
occur, there also needs to be a good understanding of how the casemix variables
impact on clinical outcomes, as well as resource use. This casemix adjustment
methodology is described in the recently published Department of Health
document,^52^ which recommends that
significant casemix variables are identified, and that the size of their relationship
with clinical outcomes is determined in advance.

**Figure 2 F2:**
[figure not shown]
Casemix classification specification.

Multilevel modelling will be undertaken to ensure that both of these steps
will be delivered in this study by determining (1) which casemix criteria are most
strongly associated with clinical outcomes, allowing for clustering at the level of
‘participant’ (where episodes occur in the same individual), at the
level of ‘model of care’ (where care is received according to similar
models), and at the level of ‘site’ (where care is delivered in a
similar way within site), and (2) which casemix criteria are the strongest cost
predictor (including per diem cost, per phase cost and total episode cost).

### Model performance

The performance of the casemix classification will be assessed in both the
development and validation data sets. Classification measures including
sensitivity, specificity, predictive values and net reclassification improvement will
be reported and cut points selected a priori. We will primarily focus on
discrimination for the classification development phase, and assess both
discrimination and calibration for the validation phase.^53^ Discrimination of the classification will be measured using
the concordance statistic and CIs (c-statistic).^54^ Calibration of the classification will be measured using calibration
plot and Hosmer-Lemeshow goodness-of-fit test.^55^

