## Abstract

**Introduction:**

Provision of palliative care is inequitable with wide variations across conditions
and settings in the UK. Lack of a standard way to classify by case complexity is
one of the principle obstacles to addressing this. We aim to develop and validate
a casemix classification to support the prediction of costs of specialist
palliative care provision.

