### Outcome

The outcome is cost of specialist palliative care (including per diem cost, per phase
cost, and total episode cost) captured by: (1) staff activity matrix in both the
development and validation phase, (2) the Palliative care Resource Use Score (PRUS)
in both phases and (3) Palliative Client Services Receipt Inventory (Pall-CSRI) in
validation phase only.

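### Performance of a cost prediction is judged mainly by measures that need a binary event; no event is defined, and apart from a calibration plot no named measure gives the error in predicted cost

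*Protocol article*

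**What the plan says.** The Abstract gives the aim as to develop and validate "a casemix classification to support the prediction of costs of specialist" palliative care. The Outcome section begins: "The outcome is cost of specialist palliative care (including per diem cost, per phase", and goes on to name total episode cost. These are amounts of money, and no event or cost category is defined as an outcome.

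The modelling follows from that. Model development says: "We will use generalised linear model (multivariate regression model) to" select variables, ranked by R-squared and P value. Statistical analysis methods adds classification and regression trees. Sample size rests in both phases on a regression R-squared of 0.13.

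Model performance then states that "sensitivity, specificity, predictive values and net reclassification improvement will", in the words that follow, "be reported and cut points selected a priori". Discrimination is to be measured by a c-statistic with confidence intervals. Calibration is to be measured by a calibration "plot and Hosmer-Lemeshow goodness-of-fit test". The main focus is discrimination in development, and both discrimination and calibration in validation. Model development promises an internal check of optimism in the "performance (calibration and discrimination) of the developed classification".

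**The concern.** The measures named do not match the outcome named. Five of them have no standard meaning for a cost in pounds until someone decides which costs count as an event. The article says that cut points will be set in advance, but not whether the cut falls on observed cost, predicted cost or class membership.

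A casemix classification is useful if the cost attached to each class is close to what patients in that class actually cost, and if the classes explain a worthwhile share of the variation. No named measure puts a number on either property. An analysis plan that followed this section faithfully would report agreement on a dichotomy still to be invented, and leave cost accuracy to visual reading of a plot.

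**Working it through.** **1. The plan's own figures.** No figure is attached to the performance measures. The related stated numbers are those in Sample size for the validation phase, and they reproduce:

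- episodes per setting: 50 + 8 × 8 = 114
- participants per setting at three episodes each: 114 / 3 = 38
- with 50% attrition: 38 / 0.5 = 76 per setting, × 3 settings = 228
- episodes: 228 × 3 = 684
- with the extra 25%: 228 / 0.75 = 304, close to the stated 300
- power to test R-squared = 0.13 with 8 predictors and n = 114: f² = 0.13 / 0.87 = 0.149; noncentrality 0.149 × 114 = 17.0 on 8 and 105 degrees of freedom; power 82.5% against the stated 80%, before any allowance for clustering.

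The study is therefore sized on the share of variance explained in a continuous outcome.

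**2. What each named measure requires.**

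| Measure in Model performance | Requires | Supplied in the article? |
|---|---|---|
| Sensitivity, specificity, predictive values | event and cut | event no; cut mentioned, object and value not stated |
| Net reclassification improvement | event | no |
| Hosmer-Lemeshow test | event probabilities, with observed and expected event counts | no |
| c-statistic | event, or a continuous outcome read as rank concordance | usable as rank concordance |
| Calibration plot | observed and predicted values | yes, usable for cost |

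**3. Where R-squared appears.** It is used in Sample size and in Model development (variable ranking). It is absent from Model performance, as are mean absolute error, root mean squared error, and calibration slope and intercept.

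**4. What rank measures leave out.** For any k > 0, multiplying every prediction p by k leaves the ranks unchanged, so the c-statistic cannot move. By contrast, R-squared = 1 − Σ(y − p)² / Σ(y − ȳ)² does change, and the slope of y on p is divided by k.

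Illustration with assumed costs: 20,000 episodes, gamma with shape 1.5, mean exp(log 300 + 0.35 z), z standard normal. High cost is taken as above the observed median, and predictions are cut at their own median.

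| Predictions | c | Sens. / spec. | R-squared | Bias in mean | MAE | Slope |
|---|---|---|---|---|---|---|
| correct | 0.666 | 0.619 / 0.619 | 0.145 | +1% | 195 | 0.99 |
| × 2 | 0.666 | 0.619 / 0.619 | −1.161 | +102% | 372 | 0.50 |
| × 0.5 | 0.666 | 0.619 / 0.619 | −0.166 | −50% | 202 | 1.99 |
| squared, rescaled to the same mean | 0.666 | 0.619 / 0.619 | −0.103 | +1% | 212 | 0.43 |

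The same invariance held with the cut at the 75th percentile (c = 0.705) and with a stronger model with R-squared 0.385 (c = 0.787 at the median cut, 0.828 at the 75th percentile). Concordance with continuous cost, computed on 5,000 of the episodes, stayed at 0.626 in the first four-row setting. The last row of the table shows why a ratio of means is not enough by itself: the overall mean is right, but the slope is 0.43.

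Sensitivity and specificity are invariant here because the predictions are cut by rank. A cut fixed in pounds would make them react to rescaling, but the article states no such cut.

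**The case against.** The strongest reply is that the same section plans a calibration plot and assesses calibration in the validation data. A plot of observed against predicted cost works for a continuous outcome and would show a uniform over-prediction at once. A reader might infer from the list that the study cannot show whether its predicted costs are right, or that its aim goes untested; the plot rules out both. What remains is that the plot has no numerical summary, and the only test beside it does not fit cost.

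The c-statistic is not a purely binary measure either. Rank concordance is defined for continuous outcomes, and its blindness to scale is true in any study, which is why it is paired with calibration. The illustration shows that general property; it is not evidence of harm specific to this plan, and its cost distribution is assumed.

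A reader might also see a contradiction between the promise to quantify optimism in calibration and the emphasis on discrimination in development. There is none: a main focus does not exclude the other, and since tree predictions are class means, in-sample class calibration holds by construction, so new data are the telling place to check it.

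Finally, the phrase about cut points, and the mention of misclassification under Missing data and data handling, suggest that categorising cost is intended. An article may leave the value of a cut to a fuller document, and the two figures are not shown. That excuses the missing value. It does not excuse naming measures that depend on an event when the only stated outcome is cost and the section does not say what is to be cut.

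**Conclusion.** The point holds in this form: most of the named performance measures do not fit the stated outcome, and no named measure quantifies the accuracy of predicted cost, although a calibration plot would display it. This is a stated choice that fits badly, not detail left for elsewhere. Explained variance is not absent from the plan, since it sizes the sample and selects variables; it is missing only where performance is judged.

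The size is qualitative. No sample-size figure changes. The invariance of rank measures to rescaling is mathematical; the particular values in the illustration rest on assumed gamma costs and assumed cuts. The conclusion assumes that the figures not shown do not define a high-cost event. If they do, the threshold measures become computable, but a numerical measure of cost accuracy would still be missing from the Model performance list.

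**What to change.** Amend the Model performance section as follows.

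- **Add** R-squared (share of cost variance explained by the classes); RMSE and MAE in pounds; observed/predicted mean cost overall and by class; and calibration slope and intercept beside the calibration plot, drawn on the cost scale.
- **State how they are obtained:** optimism-corrected in phase I, computed directly in phase II, with confidence intervals that allow for repeated episodes within patients (the plan assumes three on average).
- **Drop** Hosmer-Lemeshow and net reclassification improvement.
- **Keep** sensitivity, specificity, predictive values and any thresholded c-statistic only as secondary measures, for a stated high-cost cut, saying what is cut and at what value.

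Intervals by setting should not rest on a bootstrap over sites. The Participants section lists 10 phase I sites, of which three provide hospital advisory care (two alone, one with community care), and does not give the settings of the four added in phase II. Resampling about three clusters would not be dependable.

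The cost is wording in the analysis section. No new data and no change in sample size are needed. The change should be made before the validation data are analysed.
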